## Abstract

**Background:**

Metacognitive Training (MCT) is widely used and effective in reducing positive symptoms in psychosis. Physical exercise, such as Water Aerobics (WA), improves general health, quality of life and symptoms as a low impact activity that allows social interactions. Preliminary results suggest a relationship between dopamine and psychotic symptoms, through SP transcription factors, SP1 and SP4 biomarkers. The aims of the project are to evaluate the efficacy of a combined intervention (WA and MCT) for psychosis to improve psychotic symptoms, physical health, and transcription levels of SP biomarkers.

**Materials and methods:**

This is a unicentric randomized controlled trial of three parallel intervention groups: MCT, WA and combined intervention. The estimated sample will be 48 patients with a psychotic spectrum disorder diagnosis. The assessment will be performed at baseline and at 2-months’ follow-up. Instruments used in the assessment will include clinical, cognitive, metacognitive, social cognitive and psychosocial variables.

**Discussion:**

This will be the first study investigating the impact of the combination of MCT and WA in psychosis. Moreover, it will be the first study analyzing changes in the transcriptional biomarkers SP1 and SP4 after interventions. The results of this study may have clinical implications contributing to the improvement of treatment selection.

**Clinical trial registration:**

https://clinicaltrials.gov/, identifier: NCT05455593.

## Introduction

1

Schizophrenia and other psychotic spectrum disorders are severe mental disorders that affect around 1% of the population (Ochoa et al., 2008). Positive symptoms such as delusions and hallucinations usually respond to medication. Nevertheless, psychotic symptoms are sometimes resistant to antipsychotic medication, which is often not effective enough to achieve functional recovery (Morrison et al., 2018).

In this context, psychological treatment can help improve symptoms and functioning, even in the absence of pharmacological treatment (Morrison et al., 2014). Treatments such as Metacognitive Training (MCT) (Moritz and Woodward, 2007) have shown solid evidence for the improvement of psychotic symptoms. MCT is based on Cognitive-Behavioral Therapy and Psychoeducation, and it was developed to address cognitive biases and social cognition deficits in patients with psychosis. The focus of MCT is promoting reflectiveness on thought processes. It is widely used and effective in reducing positive symptoms, improving cognitive functioning, cognitive insight, immediate memory, and quality of life in schizophrenia (Moritz et al., 2014; Pankowski et al., 2016). Those improvements have already been established as possible in early stages of the disorder (Ochoa et al., 2017; Ruiz-Delgado et al., 2022). Moreover, previous studies have found that MCT can lead to immediate and sustained improvements in symptoms for individuals with psychosis (Moritz et al., 2014; Penney et al., 2022). In addition, evidence shows that MCT can be effective for both men and women with first-episode psychosis but target distinct aspects. Salas-Sender et al. (2020) found that after MCT, women with first-episode psychosis (FEP) experienced improvements in general symptoms, cognitive insight, and attributional style, while men showed a reduced presence of the jumping to conclusion bias.

Schizophrenia also has negative effects on general health and quality of life. In this line, physical exercise represents a promising new treatment option to complement current psychosocial and pharmacological interventions for psychosis. Evidence suggests that physical exercise can improve cardio-metabolic functioning and facilitate neurogenesis in brain areas markedly affected in psychosis (Gurusamy et al., 2018). It should be noted that metabolic syndrome is very common in patients with severe mental illnesses, seriously affecting their physical health, so physical exercise would have a beneficial impact on reducing this issue (Cortés, 2011). Regarding mental health, a recent review by Mittal et al. (2017) found that moderate-intensity physical exercise can be beneficial for improving psychotic symptoms, both positive and negative, cognition, psychosocial functioning, social stigma and motor coordination, in addition to weight loss and BMI reduction. Most previous studies were based on the implementation of aerobic-type exercises, although other exercises involving motor coordination may have similar results (Firth et al., 2016). In this line, Water Aerobics (WA) has an impact in motor coordination, and previous studies indicate that it has been effective in reducing anxiety and depression in pre-and postpartum women (Davenport et al., 2018; Mottola et al., 2018). Additionally, water immersion contributes to improving health in several ways: from cardiovascular function to skeleto-muscular pain (An et al., 2019) and fostering social relationships in a rewarding environment (Vázquez Lara et al., 2017). WA can be a promising therapy for improving the mental health of individuals with schizophrenia, as other types of physical exercise have demonstrated an improvement in cognition, clinical symptoms, and quality of life in patients with schizophrenia. While running and weight training are also beneficial for people living with schizophrenia, swimming is a low-impact activity that may be more accessible to some individuals (Firth et al., 2016; Midtgaard et al., 2021).

In the context of brain-level alterations, positive symptoms of psychosis are associated with dopamine (DA) in subcortical areas of the brain (Toda and Abi-Dargham, 2007), and with the glutamatergic pathway (Jentsch, 1999). The expression of these components is regulated by specificity protein (SP) transcription factors (Priya et al., 2013). It has been described that SP transcription factors are altered in the brain tissue of people with psychotic disorders (Pinacho et al., 2011, 2013). In FEP, reduced levels of SP1 and SP4 biomarkers have been found in circulating lymphocytes. Specifically, SP4 has been associated with improvements in symptoms in women with schizophrenia treated with raloxifene (Vila et al., 2019). Additionally, cognitive deficits have been detected in animals with reduced SP4 levels (Zhou et al., 2010). SP4 is involved in the development of dendritic trees in brain and hippocampal granule neurons (Ramos et al., 2007; Zhou et al., 2010), suggesting that SP4 might be linked to schizophrenia in the context of the theory of neurodevelopment (Zhou et al., 2010). Moreover, some studies suggest that SP4 would not only act as a high-risk gene for psychosis. Instead, it could contribute to the regulation network of other genes related to the risk of developing psychosis (Zhou, 2022). Recent literature has identified a clear relationship between the cerebellum and the prefrontal cortex via the cortico-cerebellum-thalamic-cortical circuitry, both in mice and in people with schizophrenia. Evidence shows that stimulation of the signal return from the cerebellum to the thalamus would generate improvements in psychotic symptoms (Parker et al., 2017; Brady et al., 2019; Escelsior and Belvederi, 2019). In addition, it has recently been identified that the cerebellum has dopaminergic projections toward the ventral tegmental area that would ultimately modulate the prefrontal cortex (Carta et al., 2019). This study, together with previous findings showing that SP4 and SP1 control the expression of D2 receptor in the cerebellum in schizophrenia (Pinacho et al., 2013), suggests a possible role of the transcription factors SP1 and SP4 in this circuit from the cerebellum to prefrontal cortex. Considering these pathways, it would be interesting to study the effect of an intervention that integrates stimulation of the cerebellum and cortex at the same time. The cerebellum is the area in charge of motor coordination through its connection with the motor cortex, with pathways to the prefrontal cortex that relay in the thalamus or ventral tegmental area. We expect that the stimulation of the cerebellum through motor coordination tasks such as WA could influence prefrontal cortex activity and therefore cognitive functions dependent on this area. On the other hand, MCT is an intervention aiming to improve self-reflectiveness and metacognition, which are functions associated with the prefrontal area of the brain. Therefore, we believe that the application of these interventions will exponentially improve symptoms, cognitive and metacognitive functioning, and social functionality, while also assuming an improvement in the quality of life of people with psychosis.

On one hand, we expect that WA intervention will improve physical health variables. On the other hand, we expect that MCT will improve variables related to symptoms and metacognition. Therefore, our main hypothesis is that the combined intervention will enhance the benefits of WA and MCT separately. The project will aim to evaluate the effects of each intervention, comparing the changes in the explored variables between the 3 intervention groups. Specifically, it is expected that the combined intervention will greatly facilitate an improvement in symptoms, cognition, metacognition, and psychosocial functioning. In addition, the transcript levels of the SP1 and SP4 biomarkers may change after the interventions, and it is anticipated that these changes will be even greater when the two interventions are combined.

The objectives of this project are:

To evaluate the efficacy of a combined intervention (WA and MCT) in people with schizophrenia or other psychotic disorders compared to each of the independent interventions on:Psychotic symptoms, cognition, metacognition, psychosocial functioning, and social stigmaMotor coordinationState of physical health: weight, height, BMI, abdominal circumference, blood pressure, heart rate, analysis that includes information on glucose, total cholesterol, HDL, and LDLStudy changes in the transcription levels of the SP1 and SP4 biomarkers depending on the intervention received (WA, MCT or combined intervention).Associate changes in SP1 and SP4 levels to improvements in symptoms, cognition, metacognition, social functioning, social stigma, motor coordination, and physical health status.

## Materials and methods

2

### Study design

2.1

This is a unicentric randomized controlled trial with 3 parallel intervention groups. Participating services will recruit patients, and they will be randomized to each condition. Following baseline assessment, a random number table is used to assign each patient to one of the three conditions.

Conditions are (1) MCT, (2) WA, and (3) Combined Intervention (MCT and WA). The interventions include 8 weekly sessions, lasting approximately 2 months. We will perform post-treatment assessments right after the treatment ends. Upon completion of the last assessment, patients will be offered the opportunity to participate in any of the activities, regardless of the group assigned during the 2-month intervention. Details on the flowchart of the study can be seen in Supplementary Figure S1.

### Participants

2.2

The sample consists of patients with a diagnosis of psychotic disorder, according to DSM-5 criteria (American Psychiatric Association, 2014). Inpatients and outpatients are recruited from Parc Sanitari Sant Joan de Déu Mental Health Network. Inclusion criteria are (1) diagnosis of schizophrenia, schizoaffective disorder, delusional disorder, brief psychotic disorder, schizophreniform disorder or unspecific psychotic disorder; (2) Psychopathological stability; (3) age between 18 and 60 years old. Exclusion criteria are (1) head trauma, dementia or intellectual disability (premorbid IQ ≤ 70); (2) PANSS scores of ≥5 in hostility, lack of cooperation or suspiciousness; (3) diagnosis of substance dependence disorder; (4) limitations to exercise in water, such as severe mobility problems or specific phobias related to water.

### Measures

2.3

We will collect data about clinical, cognitive, metacognitive, social cognitive and psychosocial variables. We will include a sociodemographic questionnaire. Data on antipsychotic treatment will be transformed into chlorpromazine defined daily dose. The instruments used for the assessment of clinical, cognitive, metacognitive, social cognitive and psychosocial variables are reported in Supplementary Table S1.

Molecular measures of SP1 and SP4 biomarkers will be gathered. Specifically, protein transcription factor levels and mRNA expression levels in peripheral blood mononuclear cells (PBMCs) will be obtained. Moreover, somatometric data weight (kilograms), height (meters), body mass index (BMI, in kg/m^2), body abdominal girth (centimeters) and blood pressure (mmHg). We will also measure heart rate (bpm) and metabolic parameters such as glucose levels (mg/dL), HDL, LDL and total cholesterol levels (mg/dL).

### Data collection

2.4

A trained psychologist will perform baseline and post-treatment assessments of sociodemographic, clinical, functioning, metacognitive and social cognitive variables. Each assessment will consist of 2–3 interviews. Nursing staff will take anatomical measures and conduct hemograms from the cubital vein for the separation of peripheral blood mononuclear cells. The blood will be processed by the molecular psychiatry laboratory on the same day as the hemogram and will be stored at −80°C until molecular analysis.

This study is in accordance with the World Medical Association’s Declaration of Helsinki and was approved by the Sant Joan de Déu Ethics Committee (Reference: PIC-155-21). The study will involve human participants and we will obtain informed consent prior to the start of the assessments. The staff performing the assessments, hemograms and molecular analyses will be blind to the study condition assigned to the participants. All variables will be measured at baseline and after the 2-month intervention, except the WAIS-III Vocabulary subscale, which will only be administered at baseline. After the 2-month intervention, we will collect qualitative data on patient satisfaction with the intervention, based on a questionnaire created *ad hoc*.

### Interventions

2.5

Participants who meet inclusion criteria will be randomized to one of 3 study conditions: (1) Metacognitive Training (MCT), (2) Water Aerobics (WA), and (3) Combined Intervention (MCT and WA).

Metacognitive Training (MCT): MCT consists of 8 group sessions of 1 h each and weekly frequency. Different metacognitive aspects related to the most common biases that occur in people with schizophrenia are worked on. The sessions are: attributional style, jumping to conclusions (2 sessions), changing beliefs, theory of mind and emotional recognition (2 sessions), memory errors and depression and mood. The groups are structured, include visual material, are entertaining and very participative and include discussions on how misinterpreting some situations can lead to exaggerated responses. Supplementary Table S2 shows each of the sessions of the MCT intervention.

Water Aerobics (WA): each weekly session will be 45–60 min in duration. Each activity (WA and MCT session) will take place once a week. Therefore, participants assigned to the combined intervention condition will attend both activities each week.

Participants assigned to the MCT condition will be offered WA after the completion of the study. Participants assigned to the WA condition will be offered to participate in a MCT group after the completion of the study. Participants assigned to the combined intervention condition will be offered the chance to continue participating in WA after the completion of the study, if interested.

An intervention guide will be developed in which Water Aerobics will be promoted. This guide will be elaborated by professional experts in physical activity science, physiotherapy, medicine, and sports psychology.

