### Sample size calculation

2.6

Based on previous results obtained in a MCT efficacy clinical trial (Ochoa et al., 2017) and accepting an alpha risk of 0.05 and a beta risk of less than 0.2 in a bilateral contrast, we would need 48 subjects to detect a difference equal to or greater than 1.7 units in the BCIS metacognitive variable, assuming a SD of 3.63. A loss to follow-up of 25% has been estimated.

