### Data analysis

2.7

Repeated measures models will be performed comparing the results of the three groups according to the study variables, clinical, cognitive, metacognitive, and social functioning, social stigma, motor coordination, physical health status, as well as biomarker variables. We will include as covariates those variables that show significant mean differences between groups in the baseline assessment. Additionally, we will control by sex, age, antipsychotic dose (chlorpromazine levels) and symptom severity, since these are variables that have been associated with our main outcomes.

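### The described analysis and sample size make no provision for clustering by MCT group or WA session, so between-arm error bars are too narrow if outcomes correlate within groups

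*Protocol article*

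**What the plan says.** **Allocation.** Section 2.1 (Study design) allocates each patient individually to MCT, WA or the combination.

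**Delivery.** Section 2.5 (Interventions) says that "MCT consists of 8 group sessions of 1 h each and weekly frequency" and describes interactive meetings: "The groups are structured, include visual material, are entertaining and very participative and include discussions". The discussion section again places MCT in a group setting. For WA, 2.5 gives only a weekly session and its length. The abstract and introduction credit WA with social contact, which makes a class plausible, but no class format is stated. On the third arm, 2.5 adds: "Therefore, participants assigned to the combined intervention condition will attend both activities each week". It does not say whether these patients join the same MCT groups and WA sessions as the single-intervention arms.

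**Analysis.** Section 2.7 (Data analysis) says: "Repeated measures models will be performed comparing the results of the three groups according to the study variables". The adjustments it names are variables that differ at baseline, sex, age, antipsychotic dose and symptom severity. All of these belong to the patient.

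**Sample size.** Section 2.6 states that "we would need 48 subjects to detect a difference equal to or greater than 1.7 units in the BCIS metacognitive variable". The error rates behind this are a two-sided alpha of 0.05 and a beta below 0.2, and the standard deviation is taken as 3.63. On attrition, the same section says: "A loss to follow-up of 25% has been estimated". There is no design effect. The article gives no number of groups, group size or ICC.

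**The concern.** Patients who spend eight weeks in the same discussion group, with the same therapist and the same peers, may end up more alike than patients treated apart. The same could apply to a WA class and its instructor. Individual randomisation does not prevent this, because the similarity arises after allocation, through the treatment itself.

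A model that does not know who sat with whom then counts correlated patients as separate pieces of evidence. An unusually good therapist or one disruptive member can look like an effect of the intervention. In the extreme case, where one group carries a whole arm, the intervention and that particular group are the same thing in the data, and no later analysis plan can pull them apart. The number and make-up of groups is therefore partly a design decision, and it has to be taken before treatment starts.

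**Working it through.** **1. The plan's own figure.** From 2.6: difference 1.7, SD 3.63, two-sided alpha 0.05, power 80%, loss 25%. The one-sample (pre-post) formula gives (3.63 × (1.960 + 0.842) / 1.7)² = 35.8, so 36, and 36 / 0.75 = 48. The stated 48 is thus reproduced as 36 independent patients after loss, with no clustering term. (That this is a pre-post formula although the aim is a between-arm comparison is a separate matter.)

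**2. Assumptions, none of them in the article.** Equal allocation gives 48 / 3 = 16 per arm, and 16 × 0.75 = 12 completers. One or two groups per activity, hence 12 or 6 completers per group within an arm. ICC of 0, 0.01, 0.05 or 0.10, the same for MCT and WA.

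**3. Design effect for two arms with separate groups.** DE = 1 + (m − 1) × ICC, and actual alpha ≈ 2 × (1 − Φ(1.96 / √DE)).
- m = 6, ICC 0.05: DE = 1 + 5 × 0.05 = 1.25, alpha ≈ 0.080.
- m = 6, ICC 0.10: DE = 1 + 5 × 0.10 = 1.50, alpha ≈ 0.110.
- m = 12, ICC 0.05: DE = 1 + 11 × 0.05 = 1.55, alpha ≈ 0.115.
- m = 12, ICC 0.10: DE = 1 + 11 × 0.10 = 2.10, alpha ≈ 0.176.

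**4. Three-arm test by simulation.** Null data, 12 per arm, 100,000 runs per setting. Each activity has its own group effects with variance equal to the ICC, and the residual variance is 1 − ICC. Combined-arm patients carry an MCT-group and a WA-group effect. The test is a one-way F test at 5% on one value per patient, a simple stand-in for the repeated measures comparison. Shared means that combined-arm patients sit in the single arms' groups; separate means that they have their own.

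| ICC | Two groups, shared | Two groups, separate | One group, shared | One group, separate |
|---|---|---|---|---|
| 0 | 0.050 | 0.050 | 0.050 | 0.051 |
| 0.01 | 0.054 | 0.060 | 0.062 | 0.072 |
| 0.05 | 0.073 | 0.105 | 0.115 | 0.185 |
| 0.10 | 0.103 | 0.169 | 0.190 | 0.318 |

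Runs of a few thousand give the same picture to within about one percentage point.

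**5. Does sharing groups remove the problem?** It would if two compared arms shared all their groups: a two-arm simulation of that case gives 0.045 to 0.050 for ICC 0.01 to 0.10. No pair of arms here can do so. MCT-only and WA-only have no session in common; with two groups each, their pairwise test rejects at about 0.08 (ICC 0.05) and 0.11 (ICC 0.10), as in step 3. Combined and MCT-only can share MCT groups, but the combined arm also carries WA effects. With two shared groups per activity, and MCT and WA groupings crossed in the combined arm, the rates are 0.061 and 0.075. With one shared group per activity they are 0.084 and 0.124.

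**6. What a group-level analysis can deliver.** Two separate groups in each of three arms leave 6 − 3 = 3 degrees of freedom for the group variance. With groups of 6, the chance that the variance estimate is zero or negative is P(F(3, 30) ≤ (1 − ICC) / (1 − ICC + 6 × ICC)): about 47% at ICC 0.05 and 38% at ICC 0.10. A test on 3 df needs |t| > 3.18, against 2.03 on 33 df. With 1.7 / 3.63 and 12 per arm, pairwise power falls from about 20% to 13% even when the ICC is 0.

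**The case against.** A reader might infer that the trial's standard errors and p-values are simply wrong. The documents do not support that. Section 2.7 never says that patients are treated as independent; it is silent. Repeated measures models can carry a group random effect, and neither the full protocol nor the analysis plan is shown. At ICC near 0 the unadjusted test is nominal, and at 0.01 the excess is about two percentage points at most. MCT is manualised, which may limit differences between therapists. The 32% figure needs one group per activity, separate groups and an ICC of 0.10 all at once, and the article states none of these.

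A reader might also take the combined arm's attendance at both activities as making matters worse. If those patients share groups with the single arms, it lessens the inflation in exactly the comparisons that the main hypothesis concerns. If WA sessions carry no correlation of their own and MCT groups are shared, combined versus MCT-only is about nominal. Nor is one ICC likely to fit every endpoint: no group correlation is argued for the laboratory, anthropometric or biomarker outcomes.

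All of that stands, and it limits the size of the point. It does not remove the point. The article lists its adjustment variables and fixes its sample size, and delivery group is in neither. MCT-only versus WA-only is exposed under any sharing arrangement. An arm served by a single group cannot be rescued by an analysis plan written later.

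**Conclusion.** The point holds in conditional form. MCT is delivered in participative groups and WA plausibly in classes, while the described model and the sample size make no provision for delivery group. If outcomes correlate within groups, the between-arm error bars are too narrow. With 12 completers per arm, one or two groups per activity and equal ICCs, the naive three-arm 5% test rejects at about 5% to 7% for ICC 0.01, 7% to 19% for 0.05 and 10% to 32% for 0.10. The low end of each range applies with two groups per activity that combined-arm patients share with the single arms.

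These rates rest on assumed ICCs, group numbers and a WA class format, and on a simple F test in place of the planned model. They show what could happen, not what will. The one consequence that needs no ICC figure is that an arm served by one group confounds arm with group.

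**What to change.** 1. State how many MCT groups and WA sessions will run, and whether combined-arm patients join those of the single arms. Where the existing schedule allows, plan at least two delivery groups per activity in each arm.
2. Record each patient's MCT group and WA session group.
3. Add to section 2.7 a prespecified sensitivity analysis with random effects for MCT group and WA group (set to zero for an activity that the patient does not receive) and a small-sample degrees-of-freedom correction. State that between-arm conclusions are provisional if they do not survive it.

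**Cost.** One recorded variable per activity and a short addition to 2.7. A second group may mean extra weekly sessions, which is why item 1 is tied to the existing schedule. With so few groups the variance will often be estimated as zero, and intervals that use group-level degrees of freedom are substantially wider. For that reason this is proposed as a sensitivity analysis and not as the primary model.
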